### Statistical methods

#### Treatment effect size

The Phase III of this trial will be designed to detect a prolongation of 8 months in survival. The rationale behind this assumption is as follows: CIRT is characterized by a higher RBE as compared with conventional photon radiotherapy or PRT. Preclinical experiments on glioblastoma cell lines have shown that the RBE of CIRT lies between 3 and 5, depending on the respective endpoint or cell line [52]. Further, the timing of the CIRT boost (given prior to standard PRT) is expected to overcome the tumor environmental limitations (hypoxia, radio-naïve cells, cell number, etc.) with greater cell-killing effect than conventional PRT alone. Therefore, the effect of CIRT on primary glioblastoma is expected to be substantially higher than that of conventional PRT alone.

#### Type I error rate and power

Time to death for any reason will be compared between the two arms in Phase III of this trial, using a two-tailed log-rank test at an overall type I error rate of 5%. The desired power is 80%. Sample size calculation is based on the unstratified log-rank test.

#### Sample size calculation

For calculating the OS, assuming a median OS of 16 months in the control arm and 24 months in the experimental arm (corresponding to a hazard ratio of 0.67 or a reduction in the risk of death by 33%), 192 events are required to achieve an 80% power of the log-rank test at a two-sided overall α level of 5%.

#### Anticipated duration of trial

The sample size for this trial is calculated based on the assumption of a 36-month recruitment period (with an average recruitment of 7 patients per month) and a minimal follow-up of approximately 24 months for the last patient enrolled. To observe the required number of events in the timeframe defined above, a total of 243 patients (122 in the experimental arm and 121 in the control arm) will be required. A dropout rate of 5% (12 patients) due to lost to follow-up or treatment discontinuation has been considered in the above-mentioned estimations.

#### Analytical techniques

##### Outcome analyses

The difference in duration of survival between the two arms will be tested with a two-sided, stratified log-rank test at the 5% α level. Kaplan–Meier curves will be displayed, and median survival estimates and confidence limits will be calculated. The Cox regression analyses, adjusted and unadjusted, for stratification factors will be performed in an exploratory manner. PFS will be analyzed analogously to the method for OS, but of explorative nature.

A Lan-DeMets α spending function with an O’Brien-Fleming boundary will be used at the interim analysis to maintain an overall α of 0.05. The interim analysis will be performed after 96 OS events with an α of 0.003; the primary OS analysis will be performed after 192 events with an α of 0.049.

The rates of adverse events will be summarized by the type and severity. A Fisher’s exact test will be used to compare the observed adverse events between the two arms.

The primary efficacy analysis will be performed in the intention-to-treat (ITT) population, which is defined as the population of all randomized patients, analyzed in the arm to which they have been assigned. The OS and PFS of the ITT population will be calculated. The toxicity analysis will be performed on all patients who have received at least one dose of irradiation.

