**Methods and design:**

Patients with newly diagnosed malignant gliomas will have their tumor tissue samples submitted for the analysis of the status of O-6-methylguanine-DNA methyltransferase (*MGMT*) promoter methylation. In Phase I, the patients will undergo an induction carbon ion radiotherapy (CIRT) boost followed by 60 GyE of proton irradiation with concurrent temozolomide (TMZ) at 75 mg/m^2^. To determine the maximal dose of safe induction boost, the tolerance, and acute toxicity rates in a dose-escalation manner from 9 to 18 GyE in three fractions will be used. In Phase III, GBM-only patients will be randomized to receive either 60 GyE (2 GyE per fraction) of proton irradiation with concurrent TMZ (control arm) or a CIRT boost (dose determined in Phase I of this trial) followed by 60 GyE of proton irradiation with concurrent TMZ. The primary endpoints are overall survival (OS) and toxicity rates (acute and long-term). Secondary endpoints are progression-free survival (PFS), and tumor response (based upon assessment with C-methionine/fluoro-ethyl-tyrosine positron emission tomography [MET/FET PET] or magnetic resonance imaging [MRI] and detection of serologic immune markers). We hypothesize that the induction CIRT boost will result in a greater initial tumor-killing ability and prime the tumor microenvironment for enhanced immunologic tumor clearance, resulting in an expected 33% improvement in OS rates.

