## Methods and design

### Study design

The purpose of this trial is to first determine, in a Phase I dose escalation study, the maximal safe induction CIRT boost to the residual tumor in malignant glioma patients [GBM or anaplastic astrocytoma (AA)] that can be given to patients in addition to adjuvant radiotherapy at the standard dose (i.e., 60 GyE in 30 fractions). The rationale for this approach is to provide a different form of radiotherapy; one with a higher LET, having a different mode of tumor-killing, and possessing a greater overall tumor-killing ability due to its weaker dependence on oxygenation for efficacy, to the site of disease immediately after surgery when the number of tumor cells and extent of hypoxia are at their greatest. We anticipate that these factors will result in a shift from the usual pro-tumor immunosuppression, fostered by tumor microenvironment, into one that promotes a greater inflammatory and anti-tumor immunity environment.

In the second stage of this trial, the Phase III, the following hypothesis will be tested: When induction CIRT boost with the maximal safe dose (determined in Phase I) is given prior to standard PRT, whether this strategy will result in a prolonged OS of GBM patients without provoking additional toxicity as compared with standard PRT.

A secondary aim of this study is to determine if there are immunologic response profile differences between those receiving CIRT boost and those who do not, such that additional immunotherapeutic agents can be administered in future trials to synergize and augment the effects of the CIRT boost.

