#### Phase III

The primary objective is to detect an improvement in OS in those patients who received an induction CIRT boost with no additional toxicity. The secondary objectives are to determine the response rates, progression-free survival (PFS), and tumor response (based upon assessment with C-methionine/fluoro-ethyl-tyrosine positron emission tomography [MET/FET PET] or magnetic
resonance imaging [MRI] and detection of serologic immune markers).

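### Absence of added toxicity is a primary claim, but the only planned comparison is Fisher's test of difference, which cannot establish it

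*Protocol article*

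**What the plan says.** Three places in the protocol article give toxicity primary standing.

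- Abstract, Methods and design: "The primary endpoints are overall survival (OS) and toxicity rates (acute and long-term".
- Study design: the Phase III hypothesis is longer survival "without provoking additional toxicity as compared with standard PRT".
- Phase III entry under Study objectives: "The primary objective is to detect an improvement in OS in those patients who received an induction CIRT boost with no additional toxicity".

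Under Outcome analyses the analysis is fixed. "The rates of adverse events will be summarized by the type and severity", and then "A Fisher’s exact test will be used to compare the observed adverse events between the two arms". The population is also given: "The toxicity analysis will be performed on all patients who have received at least one dose of irradiation".

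The design figures concern survival alone. Under Type I error rate and power, "Sample size calculation is based on the unstratified log-rank test", and the sections that follow give medians, deaths and patient numbers for overall survival. The article states no toxicity rate, acceptable excess, margin or power. The Follow-up section keeps patients under observation until death or indefinitely.

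**The concern.** A test of difference and a claim of no added harm point in opposite directions. Fisher's test can reject equality. When it does not, the data may still be compatible with a large excess. If the stated objective is to be answered from the stated analysis, a non-significant p-value is the only thing the article offers to rest it on.

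The question matters in this design. The boost is added to the full 60 GyE, and Table 1 puts the cumulative brain EQD2 at 67.2 to 92.4 GyE across the boost sets, against 60.0 GyE for protons alone. Phase I selects the dose on acute toxicity in groups of three to six, so Phase III is where long-term toxicity is compared between arms.

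A second issue concerns late toxicity. Counting patients who ever had an event ignores how long each was alive to have one. The trial is designed around a survival difference, so the arm that lives longer has more time in which to record late events, even if the boost adds no late toxicity at all. If the boost arm died sooner, the same mechanism would hide harm.

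**Working it through.** **Inputs from the article.** 122 experimental and 121 control patients, 36 months of recruitment, about 24 months of minimum follow-up (Anticipated duration of trial); medians of 16 and 24 months, 192 deaths (Sample size calculation); two-sided 5% (Type I error rate and power).

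**Assumptions.** All toxicity rates, hazards and margins below. Survival is taken as exponential, recruitment as uniform with analysis at month 60, and dropout is ignored.

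**1. The plan's own figure.** Deaths = 4 × (1.960 + 0.842)² / [ln(16/24)]² = 191, and 192 deaths give 80.2% power. The survival figure reproduces. There is no toxicity figure to reproduce.

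**2. Power of Fisher's test.** Power is the sum over all (x, y) of Bin(x; 122, pE) × Bin(y; 121, pC), counting only outcomes with Fisher p < 0.05.

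| Control vs experimental | Power | Missed |
|---|---|---|
| 5% vs 10% | 23% | 77% |
| 5% vs 15% | 69% | 31% |
| 10% vs 20% | 53% | 47% |
| 15% vs 30% | 77% | 23% |
| 20% vs 30% | 39% | 61% |
| 20% vs 40% | 92% | 8% |

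**3. One possible result.** With 12/121 (9.9%) against 23/122 (18.9%), Fisher's p = 0.067. The difference is 8.9 points, with SE = √(0.1885 × 0.8115/122 + 0.0992 × 0.9008/121) = 0.0446. The Wald 95% interval is therefore about +0.2 to +17.7 points. The interval just excludes zero although p > 0.05 because Fisher's test is conservative. A near-doubling would be reported as not significant.

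**4. Late toxicity: time at risk.** Death hazards are λ = ln 2/16 = 0.0433 (control) and ln 2/24 = 0.0289 (experimental) per month. Potential follow-up C is uniform on 24 to 60 months, so E[exp(−rC)] = [exp(−24r) − exp(−60r)]/(36r). Mean time at risk is (1 − E[exp(−λC)])/λ:

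- control: (1 − 0.179)/0.0433 = 19.0 months
- experimental: (1 − 0.311)/0.0289 = 23.9 months (ratio 1.26)

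Now give both arms the same late-toxicity hazard h. The crude proportion is h/(h + λ) × (1 − E[exp(−(h + λ)C)]).

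| h per month | Control | Experimental | Gap (points) | Fisher rejects |
|---|---|---|---|---|
| 0.5% | 8.8% | 11.0% | 2.2 | 5.9% |
| 1% | 16.4% | 20.3% | 3.8 | 9.4% |
| 2% | 28.9% | 35.0% | 6.1 | 15.3% |

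With truly equal proportions at these levels the test rejects about 4% of the time. Starting the hazard at month 0, 3 or 6, with a 24-month risk of 10–30%, gives rejection of about 5–14%.

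**5. Which late-toxicity measure removes the artefact.** Cumulative incidence with death as a competing event at time t is h/(h + λ) × (1 − exp(−(h + λ)t)).

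- 24 months: 13.5% vs 15.6% (h = 1%), 24.7% vs 28.3% (h = 2%)
- 60 months: 18.0% vs 23.2% (h = 1%), 30.9% vs 38.7% (h = 2%)

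These gaps arise from survival alone, so cumulative incidence does not remove the artefact. The cause-specific hazard ratio is h/h = 1 in this model.

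**6. What a margin could deliver.** With equal true rates p, SE = √(2p(1 − p)/121.5), and power is Φ(margin/SE − 1.96).

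| True rate | 5-point margin | 10-point margin |
|---|---|---|
| 5% | 43% | 95% |
| 10% | 25% | 74% |
| 20% | 16% | 50% |

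**The case against.** The best defence is that Fisher's test here is ordinary safety reporting. The sample size and the alpha plan belong to overall survival, adverse events are also summarised by type and severity, and margins, windows and estimators are often left to a full protocol or analysis plan that is not shown. A reader might infer that the trial will declare the boost free of added toxicity whenever p exceeds 0.05. No such rule is written, and that reading is not supported. What remains is that the article itself calls toxicity primary, writes its absence of increase into the hypothesis and objective, and names a test. An analysis plan that keeps the test keeps the mismatch.

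A reader might also infer that a doubling, or a 10-point rise, would usually be missed. That is not true in general: power is 69% for 5% vs 15%, 77% for 15% vs 30% and 92% for 20% vs 40%. It depends on a control rate that the article does not give.

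Nor is it right to call crude proportions biased throughout. For acute toxicity in a short, fixed window, survival hardly differs between the arms and comparing proportions is reasonable; what is lacking there is a criterion. For late toxicity, a crude proportion does answer how many patients experienced an event. It does not answer whether the treatment raises the rate of late events among patients still alive.

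**Conclusion.** The point stands. The stated analysis cannot support the stated primary claim, because a non-significant Fisher test is not evidence that toxicity was not increased. This follows from the wording alone and needs no assumed rate. The size does depend on assumed rates: power runs from 23% (5% vs 10%) to 92% (20% vs 40%) in the scenarios examined.

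The late-toxicity distortion is real but secondary and moderate. With equal hazards of 0.5–2% per month and the planned survival difference, it produces a spurious excess of about 2 to 6 points and rejection of about 6–15% against a null of about 4%. It rests on exponential survival and a constant late hazard, and it reverses direction if the boost arm dies sooner. The overall survival comparison is not affected by either point.

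**What to change.** **Acute toxicity.** Report the difference between arms in the proportion of patients with grade ≥ 3 acute toxicity, with its 95% confidence interval. Claim no added toxicity only if the upper limit lies below an excess that the sponsor fixes before comparative toxicity data are seen. If no such limit can be agreed, remove the claim from the hypothesis and objective and call toxicity a safety endpoint.

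**Late toxicity.** Base the between-arm comparison on the cause-specific hazard ratio for time to first grade ≥ 3 late event, censored at death. Show cumulative incidence with death as a competing event as description beside it, not as the test.

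**Cost.** No new data and no extra patients are proposed. The downside is that the safety claim becomes harder to make. With about 121 patients per arm, a 5-point limit has only about 16–43% power and a 10-point limit about 50–95%, depending on the assumed rate. If the limit the sponsor considers acceptable falls where power is poor, dropping the claim is the cheaper course.

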##### Biomarker analyses

Statistical analyses will also be performed to identify the associations between molecular marker profile and OS, PFS, and response rates. In univariate analysis, the log-rank test will be used to test for differences in OS and PFS between the different subgroups defined by the *MGMT* promoter methylation status and serologic marker levels. Multivariate analyses will be performed using the Cox proportional hazard model to determine if the molecular markers are independent prognostic factors and possibly predictive factors for treatment effect.

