#### Serologic immune markers

Because it is anticipated that the immune response towards GBM treated with CIRT will be distinct from the response towards tumors treated with standard, low-LET radiotherapy, peripheral blood levels of key immunologic markers will be assayed and compared with baseline levels. Several studies have reported that aberrant levels of cytokines and subtypes of circulating T cells can be detected in the blood samples of glioma patients and can serve as markers of tumor biology/immune state, virulence, and progression [46–49]. The markers to be assayed play critical roles in either the pro-inflammatory/anti-tumor or anti-inflammatory/pro-tumor immunity and are summarized in Table 2. The dual purpose of this data collection will be to both characterize the immune responses towards GBM treated with CIRT and to inform future immunotherapy trials which use this radiotherapeutic modality.

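### Testing serologic markers by log-rank between level subgroups forces nine quantitative markers into groups and loses about 36% of the information at a median split

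*Protocol article*

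**What the plan says.** The Biomarker analyses section (under Statistical methods, Analytical techniques) sets out two steps.

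- **Univariate:** "the log-rank test will be used to test for differences in OS and PFS between the different subgroups defined by the" markers. The grouping variables are named there as *MGMT* "promoter methylation status and serologic marker levels".
- **Multivariate:** "Multivariate analyses will be performed using the Cox proportional hazard model to determine if the molecular markers are independent prognostic factors", and possibly predictive ones. The section does not say whether the markers enter this model as continuous or grouped terms.

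Table 2 (Phase III, Serologic immune markers) lists nine markers: IL-1β, IL-6, TNF-α, CD3+ and CD8+ lymphocytes, IL-4, IL-10, TGF-β and regulatory T cells. Six are measured by serum ELISA and three by flow cytometry. All patients are sampled before irradiation and between the fifth and sixth proton fractions. Experimental-arm patients have one more sample between the boost and the first proton fraction.

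The section on serologic immune markers under Treatment response assessments says that "peripheral blood levels of key immunologic markers will be assayed and compared with baseline levels". It gives the purpose of the data as to "characterize the immune responses towards GBM treated with CIRT and to inform future immunotherapy trials". By contrast, the *MGMT* section records methylation simply as present or absent.

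**The concern.** A log-rank test compares groups. For *MGMT* the groups exist already. For a concentration or a cell measurement they have to be created, and every patient within a group is then treated as having the same value. If risk changes gradually with the marker, that discards information the trial has already paid to collect.

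Serologic markers appear in the Phase III secondary objectives, and the Biomarker analyses section wants to say which markers are prognostic or predictive. A method with avoidably low power would miss some graded associations that the same blood samples could have shown. The protocol already names a Cox model, which can use the measured values directly.

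**Working it through.** **Inputs from the protocol.** 243 patients (122 and 121), 36 months of recruitment, about 24 months of follow-up for the last patient, two-sided 5%, 80% power, 192 OS events, "assuming a median OS of 16 months in the control arm and 24 months in the experimental arm".

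**Assumptions, not in the protocol.** Exponential survival, no dropout, a normally distributed marker, and a log-linear effect on the hazard.

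**1. The plan's own event count.** With hazard ratio 16/24 = 0.667, the Schoenfeld formula 4(1.960 + 0.842)²/(ln 0.667)² gives 191 events (193 at the final alpha of 0.049). The stated 192 is reproduced. The protocol gives no power figure for the marker analyses.

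**2. Deaths available.** For a patient recruited uniformly over R = 36 months and followed for at least F = 24, P(death) = 1 − [exp(−λF) − exp(−λ(R+F))]/(λR), with λ = ln 2/median.

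- Control (16 months): 0.821.
- Experimental (24 months): 0.689.
- Total: 121 × 0.821 + 122 × 0.689 = 183.4.

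Simulation with a pooled median of 19.5 months gave about 184 deaths, the figure used below.

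**3. Information kept after grouping.** For a split at quantile q, the efficiency relative to a linear term is φ(z_q)²/[q(1−q)].

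| Grouping | Kept | Lost |
|---|---|---|
| Median split | 2/π = 0.637 | 36% |
| One-third / two-thirds | 0.595 | 41% |
| Quartile | 0.539 | 46% |
| Three equal groups | 6φ(z_{1/3})² = 0.793 | 21% |

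For such a marker the median is therefore the best single cut. The three-group figure is for a test for trend. An unordered three-group test spends a further degree of freedom.

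**4. Power at 184 deaths.**

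- Continuous: Φ(√184 × ln HR − 1.96).
- Median split: the first term is multiplied by √0.637 = 0.798.

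At HR 1.22 per SD, √184 × ln 1.22 = 13.56 × 0.199 = 2.70.

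- Continuous: Φ(0.74) = 77%.
- Median split: 2.70 × 0.798 = 2.15, and Φ(0.19) = 58%.

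| HR per SD | Continuous, formula (simulated) | Median split, formula (simulated) |
|---|---|---|
| 1.16 | 52% (52%) | 36% (37%) |
| 1.22 | 77% (76%) | 58% (57%) |
| 1.28 | 92% (91%) | 76% (75%) |

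The simulated values come from 4,000 runs per effect size, with 243 patients and censoring uniform over 24 to 60 months. A separate simulation (pooled median 20 months, about 183 deaths, log hazard ratio 0.2022 per SD) gave 78% against 59%, and an information loss of about 35%.

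**5. At the planned 192 events.** The effect with 80% power as a continuous term is (1.960 + 0.842)/√192 = 0.202, or HR 1.22 per SD. After a median split its power is 61%, equivalent to using 192 × 0.637 = 122 events.

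**The case against.** **The comparison favours a linear term by construction.** With a normal marker and a log-linear effect, the continuous analysis is the best available. If a marker acts through a threshold, a cut at or near it would lose less and could do better. This stands. The protocol gives neither a marker distribution nor an effect shape, so 36% is a benchmark and not a forecast.

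**A Cox model is already planned.** This also stands in part. That model may use continuous values, so the loss is established only for the univariate step. But the text does not say so, and it does fix the univariate method.

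**No cut-off is stated.** A reader might take this as the fault. It is not: cut-offs for secondary marker analyses are commonly left to a statistical analysis plan, which is not shown here. However, no cut-off supplied there would recover what grouping discards.

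**False findings from data-chosen cut-offs.** A reader might infer that cut-offs will be picked after looking at survival, which would inflate false-positive findings. The protocol states no such search. A fixed median cut kept the type I error at about 5% per marker in simulation.

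**Marker selection.** A reader might also infer that these log-rank tests will choose markers for later immunotherapy trials. The protocol says only that the marker data should describe the immune response and inform such trials.

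**Conclusion.** The point holds as an improvement to a method the protocol states. Testing OS and PFS by log-rank between level subgroups forces nine quantitative markers into groups. Under the assumptions listed, the chance of missing a true effect of 1.22 per SD rises from about 23% to about 42% at a median split. Other two-group splits do worse, three groups do better, and a real threshold effect would narrow or reverse the gap.

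The documents do not support anything stronger, either on false-positive rates or on an absent cut-off as a defect in itself. The consequence is confined to secondary marker analyses and is minor. The primary OS comparison, the 192-event calculation and the overall 5% alpha are unaffected.

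**What to change.** In the Biomarker analyses section:

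- Keep the log-rank test for *MGMT* status only.
- Analyse each serologic marker as a continuous term, log-transformed if skewed, in both the univariate and the multivariate Cox models, and report the hazard ratio per SD.
- Add a marker-by-arm term for the predictive question. It can be fitted for the samples taken in both arms, but not for the post-boost sample, which exists only in the experimental arm.
- For on-treatment values or changes from baseline, count survival from the sampling time. The protocol's OS clock starts at pathological confirmation and its PFS clock at the first day of treatment, both before those samples are drawn.
- Use grouped Kaplan–Meier curves for display only.

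The cost is a change of wording. No new data, visits or patients are needed. The downside is that a hazard ratio per SD is less familiar to clinicians than a comparison of high with low groups, which the display curves partly offset.

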##### Serologic immune markers

To ascertain the specific immune response profile to the induction CIRT boost, all patients enrolled into the Phase III study will have their blood samples investigated before irradiation to establish the baseline profile of serologic immune markers (detailed in Table 2 and between the fifth and sixth fractions of PRT to determine the changing profile. Those who receive the induction CIRT boost will have an additional serologic marker detection between the last fraction of the boost and the first proton fraction. The overall Phase III schema is illustrated in Fig. 1.

**Table 2 Tab2:** Serologic immune markers of GBM

Marker	Function/correlative findings	Assay
Pro-inflammatory/anti-tumor		
IL-1β	Stimulates cytotoxicity; serum levels decrease during low-LET radiotherapy [55]	Serum ELISA
IL-6	Pro-inflammatory cytokine, defective expression from lymphocytes in patients with glioma [56]	Serum ELISA
TNF-α	Promotes cell-directed cytotoxicity; reduced levels are associated with GBM [57]	Serum ELISA
CD3+ lymphocytes	Direct immune-mediated cytotoxicity; increased levels are associated with prolonged survival [58]	Flow cytometry
CD8+ lymphocytes	Direct immune-mediated cytotoxicity, increased levels are associated with prolonged survival [58]	Flow cytometry
Anti-inflammatory/pro-tumor		
IL-4	Induces immunosuppression and tumor tolerance; high levels are associated with GBM [57]	Serum ELISA
IL-10	Induces immunosuppression and tumor tolerance; high levels are associated with GBM [57]	Serum ELISA
TGF-β	Promotes proliferation and immune escape of GBM [59]	Serum ELISA
Regulatory T cells	Secrete IL-10 and TGF-β, suppress CD8-dependent tumor-specific cytotoxicity, and elevated in peripheral blood of GBM patients [60]	Flow cytometry

*GBM* glioblastoma, *IL* interleukin, *TNF*-*α* tumor necrosis factor-α, *TGF*-*β* transforming growth factor-β, *LET* linear energy transfer, *ELISA* enzyme-linked immunosorbent assay

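### The univariate log-rank tests by serologic marker level ignore arm; if the on-treatment blood sample defines the subgroups, a marker with no effect on survival can look prognostic because it reflects treatment

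*Protocol article*

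**What the plan says.** Under Biomarker analyses (Analytical techniques), the univariate step is that "the log-rank test will be used to test for differences in OS and PFS between the different subgroups" formed by MGMT promoter methylation and by serologic marker levels. A Cox model follows, to judge whether the markers are independent prognostic factors and "possibly predictive factors for treatment effect". Neither sentence mentions arm, stratification, an interaction term or the sample that supplies the level.

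Under Serologic immune markers (Phase III design), every Phase III patient gives a baseline sample before irradiation and a second sample "between the fifth and sixth fractions of PRT to determine the changing profile". Patients given the boost have one more sample, between the last boost fraction and the first proton fraction.

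The Study design section makes it a secondary aim to look for "immunologic response profile differences between those receiving CIRT boost and those who do not". The section on serologic markers under Treatment response assessments expects a distinct immune response after carbon ions, and the Discussion expects a shift towards anti-tumor immunity. The sample size section expects a survival benefit, "assuming a median OS of 16 months in the control arm and 24 months in the experimental arm".

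**The concern.** By the fraction 5-6 sample, the experimental arm has had the boost and the control arm has not. If the boost moves a marker, the high group contains more experimental patients and the low group more controls. If the boost also prolongs survival, high and low then differ in survival even when the marker itself does nothing. A univariate log-rank test cannot separate the two explanations.

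The immune data are meant to inform later immunotherapy trials. The error also grows in the very case where the trial succeeds and these results would be most used. A marker could be reported as prognostic when it only records which treatment the patient had.

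**Working it through.** **Inputs from the protocol.** 122 and 121 patients; 36 months' accrual; median OS 16 and 24 months, so HR = 16/24 = 0.667 and |ln HR| = 0.405; 192 deaths.

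**Assumed.** The marker is normal with no effect on survival, is shifted by δ SD in the experimental arm, and is split at the pooled median. The protocol gives no δ, so a range is shown.

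**The plan's own figure first.** The biomarker analysis has no stated figure. For the primary test the protocol says "192 events are required to achieve an 80% power of the log-rank test". Schoenfeld: 4 × (1.960 + 0.842)² / 0.405² ≈ 191; with 192 deaths the power is 80.2%. The design inputs are reproduced.

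**Closed-form check of the pooled marker test.**
1. Share above the pooled median: Φ(δ/2) in the experimental arm and 1 − Φ(δ/2) in the control arm; difference D = 2Φ(δ/2) − 1.
2. Apparent log HR of the marker ≈ D × 0.405.
3. Expected |z| ≈ D × 0.405 × √(192/4).
4. Rejection rate ≈ Φ(z − 1.96) + Φ(−z − 1.96).

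At δ = 1: Φ(0.5) = 0.691, D = 0.383, log HR 0.155 (HR 0.86), z = 0.155 × 6.93 = 1.08, rejection 19.0%.

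**Simulation.** Two independent sets, both with exponential survival: A cut at 60 months (4,000 trials per setting), B cut at the 192nd death (6,000 trials per setting for the pooled test, except 1,500 at 2 SD).

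| Shift (SD) | High, exp. / control (B) | Apparent marker HR (B) | Pooled: formula | Pooled: A | Pooled: B | Arm-stratified: A |
|---|---|---|---|---|---|---|
| 0 | 50% / 50% | 0.99 | 5.0% | – | 5.0% | – |
| 0.5 | 60% / 40% | 0.93 | 8.6% | 8.3% | 8.8% | 4.9% |
| 1.0 | 69% / 31% | 0.86 | 19.0% | 18.3% | 19.0% | 4.9% |
| 1.5 | 77% / 22% | 0.80 | 33.6% | 32.5% | 33.7% | 4.7% |
| 2.0 | 84% / 16% | 0.76 | 48.3% | – | 46.3% | – |

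In set B the arm-stratified log-rank test and the Cox model with marker and arm lie between 4.5% and 5.9% at every shift.

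**Where there is no problem.** With no shift, as for a pre-irradiation level, the pooled test holds 5.0%. With a 1 SD shift but no survival effect of the boost (HR 1.0), it rejects in 5.8% of 1,500 trials, which is nominal within simulation error (SE = √(0.05 × 0.95/1500) = 0.6 points).

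**Nine markers.** Table 2 lists nine. If all shifted by 1 SD, the expected number falsely flagged for OS would be 9 × 0.19 = 1.7, against 9 × 0.05 = 0.45.

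**Predictive part.** Under a simple shift with HR 0.667, the marker-by-arm test rejects in 4.5-5.9% of trials. It is inflated only under a further assumption: if the boost raises the marker only in patients of good prognosis (assumed half of patients, HR 0.5), it rejects in 15% (1 SD) to 32% (2 SD). Treatment then appears to have HR 0.61 against 0.79, or 0.58 against 0.91, in high against low groups, although it acts equally in all. A baseline marker in the same setting gives 5.1%.

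**The case against.** The protocol never says that the marker tests pool the arms or use on-treatment levels. Both are inferred, and a condensed article may leave covariates and sample choice to a fuller document. The baseline sample exists for all Phase III patients, and with it the test is sound. MGMT is a tumour-tissue marker that the boost does not shift. The post-boost sample is taken in one arm only, so it cannot be confounded between arms. The Cox model that follows would remove the false prognostic signal if it contained arm, and a predictive question can hardly be asked without arm. The shifts are assumed; at 0.5 SD the apparent HR is only 0.93. The analysis is secondary, and the protocol ties future immunotherapy to immune profiles as a whole, not to these survival tests alone.

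Most of this stands, and it limits the point to the univariate test on the fraction 5-6 sample. It does not remove it. The protocol does state a method: a univariate test holds the marker and nothing else, and elsewhere the article says stratified or unstratified when it means either. Nothing restricts the levels to baseline, and arm is not listed for the Cox model.

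A reader might go further and infer that a treatment-shifted marker will also look predictive. The documents do not support that: a simple shift leaves the interaction test at about 5%, and the inflation needs a marker change that depends on prognosis, which the protocol does not postulate. Nor does a high-against-low comparison become mainly a comparison of arms: at 1 SD the split is 69% against 31%.

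**Conclusion.** The concern holds in a limited form. Followed as written with fraction 5-6 levels, the univariate log-rank test is confounded by arm under the trial's own hypotheses. For a marker without any effect it would reject in about 8-9%, 18-19% or 32-34% of trials at shifts of 0.5, 1.0 or 1.5 SD, against about 5% when stratified by arm. This rests on three conditions: on-treatment levels define the subgroups, arm is left out, and the boost prolongs OS as assumed. The shift sizes are illustrative.

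Baseline levels, MGMT status, and the primary OS test with its 192 events are untouched. There is no general false predictive signal. The post-boost sample has no control counterpart and so cannot support a treatment-interaction test at all. The point concerns a secondary analysis, but the correction is simple and worth making.

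**What to change.** In Biomarker analyses:

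1. Stratify the marker log-rank tests by arm, and include arm in the Cox models.
2. Base predictive claims on the pre-irradiation level, tested by a marker-by-arm interaction.
3. Analyse fraction 5-6 levels within arm or stratified by arm, count OS and PFS from the time of that sample, and label the results exploratory.

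This changes wording only and needs no new data. The cost is a slight loss of precision from stratifying and the exclusion of the few events that occur before the sample.
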